### Study design

This is a 12-week, single-center, prospective, double-blinded, randomized, placebo-controlled clinical trial. We used the SPIRIT reporting guidelines to perfect the protocol [32], from March 2020 to December 2021. Thirty individuals with asymptomatic hyperuricemia will be randomly assigned to receive Chinese medicine or a placebo at a 1:1 ratio (Figs. 1 and 2).

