### Elimination and termination criteria

The elimination criteria are as follows: (1) serious violation of exclusion standards after enrollment, (2) not completing the experimental drug administration during the experimental period as required after enrollment, and (3) incomplete one-month follow-up and no test records available for evaluation.

The termination criteria are as follows: (1) a gout attack, (2) severe adverse events, (3) condition deteriorated and required urgent medical attention, (4) the researcher recommended test termination because of the safety of the subjects, and (5) people unwilling to continue to participate in this study for personal reasons.

We will keep in touch with the subjects who drop out to observe any subsequent adverse events and collect data.

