### Outcome measures

#### Primary outcome measure

The reduction of serum uric acid is the primary outcome measure.

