### Data collection and analysis

Within the 12-week study period, there will be 4 visits: the first at week 0, the second at 4 weeks ± 3 days, the third at 8 weeks ± 3 days, and the fourth at 12 weeks ± 5 days. The data collection and completion of the CRF will be performed by two research assistants who will be blinded to the grouping of the participants. The EPIdata3.1 database software package will be used to establish a database for data entry, and double input data will be used for data entry.

The clinical trial monitors will check the quality of data entry regularly. The database after verification will then be checked by logic inspection, and the outliers will be checked with the original laboratory documents, and the final checked database will be converted into an DATABASE in the format of the SPSS statistical software package and locked for statistical analysis.

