### Statistical analysis

All statistical tests will be two-sided, and *α* = 0.05 will be considered statistically significant.

We will use a *t*-test (or Wilcoxon matched-pairs signed-ranks test if the data are non-normally distributed with uneven variances) to compare the decrease in uric acid between two groups.

For secondary outcomes, the *t*-test and Wilcoxon test will be conducted to compare the differences in measurement data (such as index mean, standard deviation, and median) between the groups. Repeated measures analysis of variance will be used to compare multiple measures of the scale and symptom rating among groups. The chi-square test (or Fisher’s exact test) and 3×C table will be utilized to determine the differences in the proportion, frequency, and total effective rate of the indices in the Chinese medicine group and placebo group.

To analyze the influencing factors of curative effects, non-conditional logistic regression analysis will be performed. For missing data from long-term follow-up, the last carry-over method (LOCF) will be used.

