## Discussion

The guidelines in different countries vary regarding asymptomatic hyperuricemia, which can lead to gout and other diseases. Social and ethnic backgrounds as well as the different development of medical ideas may prone to these differences [6]. The lack of double-blinded randomized controlled trials is another major factor. Additionally, the benefit-risk ratio of pharmacological treatments (such as febuxostat and allopurinol) is an issue that clinicians should consider. Thus, the aim of our research is not only to determine the effect and mechanism of Chinese medicine in the treatment of asymptomatic hyperuricemia but also to provide more evidence-based research for clinical work.

Based on previous years of clinical experience and cross-sectional investigation and analysis, the motive for this study is to carry out pre-research to proceed with a study aimed at people with hyperuricemia and dampness syndrome in Gouangdong; on the basis of the pre-research, the sample size will be expanded and the randomized controlled double-simulation clinical trial will be conducted to obtain high-level evidence-based research of Chinese medicine in the treatment of hyperuricemia and dampness syndrome and thus form an effective early Chinese medicine intervention plan for the population with hyperuricemia and dampness syndrome. Through this pilot study and further large-scale research, we want to provide more effective and low-risk treatment options to benefit patients. We hope to determine whether controlling the level of serum uric acid by using Chinese medicine can prevent or delay gout and other complications to reduce the pain and medical costs of patients.

As a pilot study, the limitations are obvious. There will be bias due to the small number and single data source. As the first double-blinded, randomized, placebo-controlled clinical trial to study the treatment of asymptomatic hyperuricemia with Chinese medicine, we are still not sure whether the follow-up period is long enough to see the decoction take effect. There are more questions that need to be studied, such as the level of serum uric acid needed for Chinese medicine intervention, when to withdraw the decoction, and whether the benefits of treatment with Chinese medicine can outweigh the potential medical costs in the long term. We assume that in the future, there will be more formulae and decoctions proven effective or explored.

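### LOCF is the only missing-data method named for a 12-week trial; it distorts the week-12 uric acid difference if response is still changing or drop-out differs by arm

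*Protocol article*

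**What the plan says.** The Statistical analysis section deals with missing data in one sentence: "For missing data from long-term follow-up, the last carry-over method (LOCF) will be used". The article names no other method and no sensitivity analysis.

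The primary outcome is given as "The reduction of serum uric acid is the primary outcome measure", and a t-test (or a Wilcoxon alternative) is to be used "to compare the decrease in uric acid between two groups". Neither sentence names a time point, so I read week 12 from the last visit.

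Study design states: "This is a 12-week, single-center, prospective, double-blinded, randomized, placebo-controlled clinical trial". Data collection and analysis sets out four visits as follows: "the first at week 0, the second at 4 weeks ± 3 days, the third at 8 weeks ± 3 days, and the fourth at 12 weeks" (window 5 days). No later follow-up is described.

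On the length of follow-up, the Discussion says: "we are still not sure whether the follow-up period is long enough to see the decoction take effect".

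Two other sections bear on the point. Sample size says that the later large trial will be sized from this trial's main outcome results. Elimination and termination criteria removes subjects who do not complete the trial drug as required (criterion 2) and, separately, those with "3) incomplete one-month follow-up and no test records available for evaluation".

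**The concern.** LOCF assumes that a subject's uric acid would have stayed at its last observed value until week 12. The authors themselves are unsure that 12 weeks is long enough to see an effect, so a flat course from week 4 or week 8 is not something they can take for granted. If response is still building, an earlier value understates the week-12 response, and the group difference shrinks even when drop-out is random and equal in both arms.

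If drop-out is unequal and both arms drift over time, for example through diet, repeated contact or regression to the mean, LOCF produces a difference where the drug has none. LOCF also enters filled values as if they had been measured, so the standard error does not reflect the missing information.

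The estimated difference and SD are meant to feed the next trial's sample size, so an error here would carry forward.

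**Working it through.** **Inputs from the article.** 15 per arm (Abstract, Methods); two-sided 0.05 (Statistical analysis); visits at weeks 0, 4, 8 and 12. There is no planning figure to reproduce: the 30 subjects come without effect size, SD, power or drop-out rate, and the α of 0.025 and β of 0.2 under Sample size belong to the later trial.

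**Assumptions.** Drop-out m of 20% or 30%; last value at week 4 for all drop-outs, or at week 4 or 8 with equal chance; the time courses shown below; SD = 1. The readable text does not say that uric acid is measured at weeks 4 and 8 (Fig. 2 is not shown); steps 1 to 3 assume that it is.

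**Step 1: equal drop-out, real effect.** Let r be the average share of the week-12 effect already reached at the last observed visit. Share kept = (1 − m) + m × r, so share lost = m × (1 − r).

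| Time course (share at week 4, week 8) | Last visit | r | Lost at 20% | Lost at 30% |
|---|---|---|---|---|
| Linear (1/3, 2/3) | all week 4 | 1/3 | 13% | 20% |
| Linear (1/3, 2/3) | week 4 or 8 | 0.5 | 10% | 15% |
| Late (0, 0.25) | week 4 or 8 | 0.125 | 17.5% | 26% |
| Early plateau (0.9, 1) | week 4 or 8 | 0.95 | 1% | 1.5% |

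If uric acid is measured only at weeks 0 and 12, carrying baseline forward gives r = 0, and the loss equals the drop-out rate, 20% or 30%.

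**Step 2: power.** The standard error of the difference is √(2/15) = 0.365 SD. The detectable difference at 80% power is (1.96 + 0.84) × 0.365 = 1.02 SD. If that is the true week-12 effect, 20% drop-out under linear build-up (week 4 or 8) leaves 1.02 × 0.90 = 0.918 SD and power Φ(0.918/0.365 − 1.96) = 71%. Late build-up leaves 1.02 × 0.825 = 0.84 SD and 64%; an early plateau leaves 79%. Not all of this is LOCF's doing: an unbiased analysis of 15 × 0.8 = 12 per arm has a standard error of √(2/12) = 0.408 SD and power Φ(1.02/0.408 − 1.96) = 70%. The case against LOCF is bias rather than power.

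**Step 3: unequal drop-out, no drug effect.** Suppose both arms fall by c SD over 12 weeks, linearly. False difference = (difference in drop-out) × (1 − r) × c.

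- 30% v 10%, c = 1, all at week 4: 0.20 × 2/3 = 0.13 SD; simulated type I error 6.3-6.4%.
- 30% v 10%, c = 1, week 4 or 8: 0.20 × 1/2 = 0.10 SD; simulated 5.7%.
- 30% v 10%, c = 0.5: half these biases; simulated 5.4% or less.
- 20% v 20%: zero; simulated 5.0%.

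The arm that loses more subjects appears to have fallen less, so the sign depends on which arm that is.

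**Step 4: the next trial.** With a two-means formula, n is proportional to 1/(difference)². With the SD held fixed, a difference understated by 10% inflates n by 1/0.9² = 1.23, and one understated by 20% by 1/0.8² = 1.56. A false difference in the drug's favour would make the next trial too small.

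**Step 5: LOCF beside the elimination rules.** Criterion 3 removes subjects with no usable records after entry, who have no later value to carry. Criterion 2 removes subjects who did not complete the drug; many who leave after week 4 or 8 fall here, and LOCF would otherwise fill them in. A subject who completed treatment but missed the week-12 visit falls under LOCF alone. The overlap is with criterion 2, and it is partial.

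**The case against.** **Scope.** The sentence limits LOCF to long-term follow-up and does not mention the primary outcome. The wording is loose, but the article describes no period after week 12, so the trial visits are the only place the rule can act.

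**The Discussion gives no trajectory.** A reader might infer that the authors expect the effect still to be emerging at week 12. They say only that they doubt the follow-up is long enough. That fits equally with no effect at any visit, in which case LOCF costs nothing in the contrast if drop-out is equal. Linear growth is my assumption, and with an early plateau the bias is negligible. This stands, and it is why the size is given as a range.

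**Small against the noise.** A bias of 0.10-0.13 SD is about a third of the 0.365 SD standard error in a 30-subject pilot. That is fair, but a larger bias cannot be ruled out and a better method costs little.

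**Stronger readings that the text does not support.** A reader might infer that LOCF and elimination are two incompatible rules for the same people. Criterion 3 does not show this, and criterion 2 overlaps only in part. A reader might also infer that anyone with a baseline value alone is scored as no change; on its natural reading, criterion 3 removes such subjects. The two harms should not be counted twice: whoever is eliminated is not also biased by LOCF. Elimination is a separate selection problem and no cure.

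**The ANOVA.** For the scale scores the article says: "Repeated measures analysis of variance will be used to compare multiple measures of the scale and symptom rating among groups". Nothing in the text shows a defect in that choice beyond possible reliance on filled values, so I do not ask for it to be replaced.

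**Conclusion.** The point holds as a recommended change. LOCF is fixed as the sole named method, acts on a 12-week schedule, and rests on a flat-course assumption that the authors' own doubt leaves unsupported.

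Under linear build-up, 20% (30%) drop-out costs about 10-13% (15-20%) of the week-12 difference. The loss is greater with a late effect and about 1-2% with an early plateau. Under no drug effect, with 30% against 10% drop-out and a shared 1 SD fall, it adds about 0.10-0.13 SD in either direction and raises type I error from 5% to about 6%. With equal drop-out and no drug effect there is no bias.

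Every size rests on assumed drop-out, SD and time course, because the article gives none. The direction of the bias is known only for a growing effect with equal drop-out, where it is toward no difference.

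**What to change.** For the primary outcome, replace LOCF with a likelihood-based mixed model for repeated measures on all observed post-baseline uric acid values. Include treatment, visit, treatment-by-visit and baseline, and report the week-12 contrast. Keep LOCF at most as a sensitivity analysis.

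If uric acid is measured only at weeks 0 and 12, analyse the observed week-12 values with baseline adjustment and do not carry baseline forward.

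State the missing-at-random assumption openly. Some of the listed reasons for termination (gout, serious harm, deterioration) may be related to outcome, so the assumption is open to doubt here.

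Say which rule governs a subject who did not complete the drug but has uric acid values: elimination under criterion 2, or inclusion with missing visits. Say also that the missing-data rule concerns visits up to week 12.

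The cost is a few sentences and a little programming; mixed models are available in SPSS and SAS. Trial conduct does not change. The downside is the missing-at-random assumption, which the data cannot verify.

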### Safety analysis

Safety data consist of adverse events and clinical laboratory tests. We will describe specific manifestations of adverse reactions and compare the incidence of adverse events and severe adverse events between the two groups. Changes in laboratory test results before and after the test, abnormal changes, and their relationship with Chinese medicine will be analyzed.

### Compliance analysis

The compliance among the subjects included in the study will be analyzed by descriptive analysis, while an intergroup descriptive analysis will be performed on the baseline information of the drop-out cases in both groups.

### Adverse events management

The type, degree, occurrence time, duration, treatment measures, treatment process, and follow-up results of adverse events that occurred during the trial will be recorded in the case report form, and the correlation between the adverse events and the experimental drugs will be evaluated on the basis of comprehensive consideration of the complications and combined use of drugs, which will also be recorded in detail by the physician.

For non-serious adverse events, the observation physician may decide whether to suspend observation based on the disease condition. Cases in which drugs are withdrawn due to adverse events will be followed up and the lab security indicators will be reexamined.

For serious adverse events, drug use will be stopped immediately. Regardless of whether it is related to the experimental drug, the investigators will report to the Ethics Committee of Guangdong Province Hospital of Chinese Medicine within 24 h after its occurrence.

If a serious adverse event occurs during the course of the study, the research team and the hospital will be responsible for subsequent treatment and financial compensation.

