#### Secondary outcome measures

The secondary outcome measures are as follows: (1) Chinese syndrome score, measurement of the channels and collaterals, and tongue diagnosis evaluation; (2) glomerular filtration rate, urinary β2 microglobulin, and uric acid excretion fraction; (3) incidence rate of complications, such as gout, hyperlipidemia, cardiovascular events, diabetes, etc.; (4) ultrasound of both ankles and the first metatarsophalangeal joints [34]; (5) evaluation index of metabolites, including blood and urine metabolites; (6) inflammatory index: hsCRP, TNF-a, IL-6, and IL-8; and (7) intestinal microecology (note: this index is tested by a separate participant).

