### Security indicators

Security indicators include the following: (1) liver function (alanine aminotransferase ALT, aspartate aminotransferase AST) and renal function (blood urea nitrogen, creatinine); (2) routine blood tests, routine urine tests, routine stool tests + occult blood; and (3) an electrocardiogram and ultrasound of the urinary system.

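### The article does not commit to measuring serum uric acid, the primary outcome, at the remaining visits of subjects who stop study drug

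*Protocol article*

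**What the plan says.** The Primary outcome measure section reads: "The reduction of serum uric acid is the primary outcome measure". Visits fall at weeks 0, 4, 8 and 12 (Data collection and analysis).

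On adverse events (Adverse events management), after a non-serious event "the observation physician may decide whether to suspend observation based on the disease condition". The next sentence adds: "Cases in which drugs are withdrawn due to adverse events will be followed up and the lab security indicators will be reexamined". The Security indicators section lists "liver function (alanine aminotransferase ALT, aspartate aminotransferase AST) and renal function (blood urea nitrogen, creatinine", then "routine blood tests, routine urine tests, routine stool tests + occult blood; and (3) an electrocardiogram and ultrasound of the urinary system". Serum uric acid is in neither part of that list.

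On leaving the trial (Elimination and termination criteria), a gout attack and a severe adverse event are termination criteria, and failing to complete the drug as required is elimination criterion (2). The section closes: "We will keep in touch with the subjects who drop out to observe any subsequent adverse events and collect data". The Secondary outcome measures include the "incidence rate of complications, such as gout, hyperlipidemia, cardiovascular events, diabetes, etc".

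Under Blinding, a subject unblinded after a serious event is terminated and receives treatment and follow-up. The only analysis set named for that subject's data is the safety set. Under Statistical analysis, LOCF is the rule for missing long-term follow-up data.

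**The concern.** The article does address what happens after drug is stopped for an adverse event. It names the tests to be repeated, and the primary outcome is not one of them. A site working from this text has an instruction to take safety blood but none to measure uric acid in it.

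Who is affected matters more than how many. Stopping for intolerance may depend on the treatment, and a gout attack is related to uric acid itself. If values are missing in these subjects, the comparison moves away from all randomised subjects towards those who tolerated the decoction. Values that were never drawn cannot be recovered by a later choice of analysis set or imputation, so an analysis plan cannot repair this part.

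The complication outcome has the same weakness. A first gout attack counts as an event, but it is also a reason for termination, and nothing states that the other complications are still recorded afterwards.

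**Working it through.** No figure in the plan depends on this point. The sample of 30 (15 per group) comes without an effect size, SD or drop-out rate, so there is nothing to reproduce. The check is first one of reading.

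**Step 1: each route off drug, and whether serum uric acid is named.**

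| Route | What the article says follows | Serum uric acid |
|---|---|---|
| Drug withdrawn for an adverse event | Follow-up; safety tests repeated | Not named |
| Non-serious event, observation suspended | Physician's decision; no tests specified | Not named |
| Unblinded after a serious event | Terminated; safety set; treatment and follow-up | Not named |
| Gout attack, severe event, deterioration, researcher's advice, own wish | Contact; adverse events and unspecified data | Neither named nor excluded |
| Incomplete dosing | Elimination | Use of later values not stated |

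**Step 2: is there a general commitment elsewhere?** The visit schedule makes no exception for subjects off drug, but it does not say that it continues for them either. No section states that uric acid is, or is not, measured after stopping.

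**Step 3: what could follow for the estimate (illustration only).** Assumptions: s of the 15 active subjects stop, none stop on placebo, the effect is D in those still on drug, and stoppers return to baseline (effect 0) by week 12.

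Effect in all randomised subjects = D × (15 − s)/15:
- s = 2: 13/15 = 0.87D
- s = 3: 12/15 = 0.80D
- s = 4: 11/15 = 0.73D

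What the trial would report depends on handling:
- Stoppers eliminated: D. Overstatement = 15/(15 − s) − 1 = 15%, 25%, 36%.
- LOCF, last value taken on drug at full effect: D, with the same overstatement.
- LOCF, stopped before week 4 so that baseline is carried forward: 0.87D, 0.80D, 0.73D. No overstatement.
- Uric acid measured after stopping and kept: 0.87D, 0.80D, 0.73D. No overstatement.
- Uric acid measured after stopping, but the subject removed under elimination criterion (2): D again.

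The last line shows that collecting the values is not enough if the elimination rule then discards them.

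**Step 4: knock-on for the later trial.** The Sample size section will size the large trial from this pilot's primary result. With the SD fixed, required n is proportional to 1/D². Where D is reported in place of the diluted effect, planned n over needed n is ((15 − s)/15)² = 0.75, 0.64, 0.54. The later trial would be about 25%, 36% or 46% too small for the effect in all randomised subjects.

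**Step 5: precision, if subjects without a value are dropped from both arms.** Difference detectable with 80% power at two-sided 0.05 (normal approximation) = (1.960 + 0.842) × √(2/n), in SD units:
- n = 15 per arm: 1.02 SD
- n = 12 (20% lost): 1.14 SD
- n = 10 (33% lost): 1.25 SD

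For an assumed true difference of 1.0 SD, power is 78%, 69% and 61%. The loss rates and the effect are assumptions.

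**The case against.** A reader might infer that only safety tests are done after stopping and that the primary endpoint is therefore not measured. The text does not support this. The word only is not there. The sentence on drop-outs promises data as well as adverse events and does not limit them. Naming safety tests in a section on adverse events is natural and does not say that other tests cease.

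Nor does the article treat stopping drug and ending observation as a single act throughout. Follow-up is promised after withdrawal for an adverse event and even after unblinding. Suspending observation is mentioned for non-serious events only, and to suspend is not necessarily to end.

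A reader might also take 15% to 36% as the expected bias. It is not. It needs stops in one arm only, full return to baseline, and either elimination or an on-drug value carried forward. Under LOCF with early stops it vanishes.

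Finally, this is an article condensing a fuller protocol, its participant timeline figure is not available here, and the trial is a 30-subject pilot. The full protocol may settle the matter.

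All of this stands and limits the claim. It does not remove the point: where the article specifies post-withdrawal tests, it omits the primary outcome; where it promises more, it leaves the content undefined; and elimination criterion (2) works against keeping such values.

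**Conclusion.** The concern holds as a missing commitment, not as a demonstrated failure to measure. The article gives no undertaking to collect serum uric acid at the remaining week 4, 8 and 12 visits after drug is stopped. It names safety tests without uric acid for adverse-event withdrawals and leaves the data on other drop-outs undefined. With gout attacks and severe adverse events as grounds for termination, and incomplete dosing as grounds for elimination, primary-outcome values may be missing or discarded in subjects whose stopping is related to treatment or outcome.

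The size of any bias is unknown. It depends on how many stop, when, in which arm, and whether LOCF or elimination is applied. Under the stated assumptions it lies between nil and a 36% overstatement. I rate this a worthwhile, cheap improvement, not a flaw that invalidates the trial.

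**What to change.** - In Elimination and termination criteria and in Adverse events management, separate stopping study drug from leaving the study. State that, unless consent is withdrawn, a subject who stops drug for any reason stays on the scheduled visits, with serum uric acid and the complication outcomes collected, and define the data to be collected from drop-outs in these terms.
- Add serum uric acid to the blood tests repeated after an adverse-event withdrawal.
- State that these values enter the primary comparison of all randomised subjects and are not removed by elimination criterion (2).
- Reconcile the wording on suspending observation with the follow-up promised in the sentence after it. No clinical rule for stopping drug needs to change.

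The cost is protocol wording, one analyte on blood already drawn, and a few extra visits by subjects off drug. Tests are already free and travel is already subsidised.

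Trial status gives enrolment as March to August 2021, so collection may be over. In that case, report which post-discontinuation uric acid values exist, by arm and visit, and carry the wording into the later large trial.
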